**Fig. 1 Fig1:**
[figure not shown]
Schedule of enrolment, interventions, and assessments. WFNS World Federation of Neurological Societies

### Sample size

We estimated a sample size of 80 randomized patients to give 90% power at the 5% significance level (two-sided) to detect a treatment effect equivalent to an absolute increase of 7% in the proportion of patients with a favorable outcome (30-day mortality rate after subarachnoid hemorrhage approaches 40% and 25% of survivors present some degree of neurological morbidity [24]). This calculation was based on an ordinal analysis of the 6-month mRS (the primary outcome), assuming that the treatment effect follows a proportional odds model.

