## Background

Subarachnoid hemorrhage from a ruptured intracranial aneurysm is a common type of stroke and is of substantial clinical and socioeconomic relevance, affecting about 600,000 patients worldwide every year. Subarachnoid hemorrhage accounts for a great deal of death and disability, particularly because it affects a younger age group than other stroke subtypes. Combined morbidity and mortality reach up to 50%, with 30% of survivors remaining dependent. Additionally, 20–30% of patients in hospital admission, initially with a good clinical grade, can have poor outcomes. These high rates of morbidity and mortality are mainly related to the extent of bleeding and other complications, including cerebral vasospasm. Clinical treatment has been largely ineffective at improving the outcome. A selective calcium channel blocker (nimodipine) remains the only evidence-based option in the management of subarachnoid hemorrhage, although with limited benefits. Conversely, delayed ischemic deficits represent the main source of neurological disability after cerebral aneurysm rupture, and prevention of cerebral arterial vasospasm constitutes a key target for new pharmacological treatments. Other options include statins and magnesium sulfate. However, recent trials have been unable to demonstrate any clinical benefits.

There is experimental and clinical evidence that sulfonylureas may be beneficial for patients with acute ischemic stroke. The pleiotropic neuroprotective effects of glibenclamide have been well substantiated over the past decade in clinically relevant models of human disease. Glibenclamide protects the microvascular endothelium to reduce the formation of edema and secondary hemorrhage, inhibits neuronal cell death, and exerts potent anti-inflammatory effects and promotes neurogenesis. Retrospective studies of patients with diabetes, as well as a recent Phase IIa pilot study in nondiabetic individuals, suggest a highly promising translational potential for therapeutic intervention with glibenclamide in ischemic stroke.

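### Eighty patients cannot give 90% power for a 7-point gain in favorable outcome; on the event rates the protocol quotes, power is about 11%

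*Protocol article*

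**What the plan says.** The Sample size section gives a complete power statement. On size, power and significance level: "We estimated a sample size of 80 randomized patients to give 90% power at the 5% significance level (two-sided) to detect a treatment effect". On the effect: "equivalent to an absolute increase of 7% in the proportion of patients with a favorable outcome". On the method: "This calculation was based on an ordinal analysis of the 6-month mRS (the primary outcome), assuming that the treatment effect follows a proportional odds model".

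The only outcome rates given with the calculation are: "30-day mortality rate after subarachnoid hemorrhage approaches 40% and 25% of survivors present some degree of neurological morbidity". The Background adds a second, similar picture: "Combined morbidity and mortality reach up to 50%, with 30% of survivors remaining dependent".

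Elsewhere the article defines favorable as mRS 0–2 and unfavorable as mRS 3–6 (Abstract, Expected outcomes), sets 1:1 allocation (Intervention), and says that a common odds ratio below 1 favors glibenclamide (Statistical analysis). It does not give the control favorable rate, the control mRS distribution or the odds ratio behind the 80.

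**The concern.** A 7-point difference in a proportion near one half is a small effect, and trials of 40 per arm do not detect small effects with high power. An ordinal analysis gains something over a dichotomy, but not a factor of twenty.

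The Discussion presents the trial as a test of clinical effectiveness meant to establish the drug's role. If the planned effect is real and power is about 11%, the trial will miss it about 89% of the time. A reader who trusts the stated 90% could then take the null result as evidence against benefit. If the true effect is 7 points, a significant result can arise only when the estimate is well above the truth.

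**Working it through.** **Inputs.** N = 80 in total, 1:1; two-sided α = 0.05; target power 90%; gain of 7 percentage points; proportional-odds ordinal analysis. All are stated in Sample size and Intervention.

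**Control favorable rate (derived).** 40% die, and 25% of the 60% who survive are impaired: 0.60 × 0.75 = 0.45. Treated rate: 0.45 + 0.07 = 0.52. This counts any survivor morbidity as mRS 3–5, and it uses 30-day mortality for a 6-month outcome.

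**Common odds ratio.** (0.52/0.48) / (0.45/0.55) = 1.324; ln OR = 0.2807. In the protocol's direction, 1/1.324 = 0.76.

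**Power by the Whitehead formula.** V = (N/12)(1 − Σp̄³), where p̄ is the mean of the two arms' category probabilities. Power = Φ(|ln OR|·√V − 1.96), plus the small opposite tail.

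- Assumed control mRS 0–6: 0.135, 0.18, 0.135, 0.05, 0.05, 0.05, 0.40 (favorable mass split 30/40/30, 40% dead).
- Treated distribution under OR 1.324: 0.171, 0.207, 0.142, 0.050, 0.048, 0.047, 0.335.
- Σp̄³ = 0.0635, so V = (80/12) × 0.9365 = 6.24 and √V = 2.499.
- 0.2807 × 2.499 = 0.701. Φ(0.701 − 1.96) = 0.104; with the opposite tail (0.004), power = 0.108.
- With 30% dead and the remainder spread over mRS 3–5: Σp̄³ = 0.0353 and power = 0.110.

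The choice of distribution hardly matters. Setting Σp̄³ to zero, which no real scale can better, still gives only about 11%. A Mann–Whitney simulation (10,000 trials of 40 per arm for each of three control distributions) gave 10.6–10.7%. A two-proportion comparison gives 9.1%.

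**Sample size for 90% power.** N = 12(1.96 + 1.2816)² / [(ln OR)²(1 − Σp̄³)]

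- 40% dead: 126.1 / (0.0788 × 0.9365) ≈ 1,709.
- 30% dead: about 1,659.
- Two-proportion formula: about 2,140.
- Shortfall: 1,709/80 ≈ 21-fold.

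**Attempts to reproduce the 90%.** At a 45% control rate:

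| Variant | Power |
|---|---|
| One-sided α | 17–18% |
| 80 per arm rather than 80 in total | about 17% |
| 7% as a relative gain (45% to 48.15%), binary | about 5% |

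Keeping the stated design and varying the control favorable rate (same 30/40/30 split of favorable scores):

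| Control favorable | OR for +7 points | Power, N = 80 | N for 90% power |
|---|---|---|---|
| 30–60% | 1.32–1.37 | 11–12% | about 1,345–1,710 |
| 75% | 1.52 | 18% | about 770 |
| 80% | 1.67 | 25% | about 512 |
| 85% | 2.03 | 42% | about 275 |
| 90% | 3.59 | 87% | about 87 |

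The stated figure is approached only with about 90% of controls favorable.

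**What 80 patients can detect.** Setting |ln OR|·√V = 3.2415 gives OR ≈ 3.6 (3.60–3.64 over the assumed distributions), or 0.28 in the protocol's direction. From 45% favorable: 0.818 × 3.6 = 2.95 odds, or 2.95/3.95 ≈ 75%. The expected 95% CI extends by a factor of exp(1.96/√6.24) ≈ 2.2 either side of the estimate.

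**The case against.** The strongest reply is that the 45% is not the protocol's figure. It is built from a 30-day mortality rate for subarachnoid hemorrhage in general, and it treats any morbidity as unfavorable although mRS 1–2 can include symptoms. The trial population is also selected: Eligibility criteria excludes Hunt and Hess V, prior dependence and age over 70, and admits patients up to 96 h after the bleed. The Background says that 20–30% of patients admitted in good grade do poorly, which would mean 70–80% favorable. On that view 11% is the low end, and a fairer range is roughly 11–25% power and 500–1,700 patients.

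It is also fair to say that the text does not show which of the three figures (80, 7 points, 90%) is wrong. The quoted 40% mortality does not strictly exclude a much better rate in selected patients. An article need not print the assumed mRS distribution if a fuller protocol holds it.

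The point about the derived rate stands as a caveat on the exact number. None of this rescues the claim. At 80% favorable, power is still 25%. A rate near 90% is better than even the good-grade figure in the Background and far from the rates cited in support of the calculation. Covariate adjustment would have to supply about 21 times the information. The fault lies in stated numbers that conflict with one another, which no unseen document can cure.

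**Conclusion.** The concern holds and must be fixed. The power statement is wrong as written: at a control favorable rate of 45%, power for a 7-point gain is about 11% (9% if dichotomized), against 90% stated, and the sample size is about 21 times too small for that effect. The exact figure rests on the derived 45%, on proportional odds (the protocol's own assumption) and, to a negligible degree, on the assumed mRS distribution. The conclusion that 90% is unattainable holds for every control rate from 30% to 85%.

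**What to change.** Keep 80 patients and correct the Sample size text. Suggested wording, with the 45% labelled as an assumption: *Assuming that 45% of control patients have a favorable outcome, 80 patients give 90% power at two-sided 5% to detect a common odds ratio of about 0.28 (favorable outcome about 45% to 75%). Power for a 7-percentage-point increase is about 11%.* Give the assumed control mRS distribution alongside it. If the sponsor's calculation used a different distribution or odds ratio, state those instead and recompute all three figures from them.

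Describe the trial as exploratory. Keep the planned common odds ratio with its 95% CI as the main result, and add that a non-significant result is not evidence of no effect.

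The cost is rewording of the sample-size and discussion text. No patients or procedures change, which matters because Trial status reports 36 patients already recruited. The price is a less favorable power statement and a more modest claim for the trial.

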### Allocation

A computer-generated randomization code will be used to randomize medication bottles by blocks of ten (five glibenclamide, five placebo). Each bottle will be identified by a specific code number and subsequently selected for distribution in an ascending numerical order. All bottles are created, coded and stored at the study center’s pharmacy by one of the staff members who does not participate in the enrolment process.

One of the investigators will enroll recruited patients and assign them one of the random bottles. Drug administration will be provided by the nursing staff, who are also blinded, together with the rest of the patient’s other medications.

### Blinding

All participants, including patients, investigators, neuropsychologists and the center’s medical and nursing staff, are blinded and have no access to the meaning of the coding. The only exception to this is one of the investigators, who had prepared the coded bottles, who will not be blinded and will monitor possible adverse effects off the main drug, as discussed in more detail below. All patients have the right to withdraw at any stage of the study and learn their allocation.

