## Study design

Glibenclamide in aneurysmatic subarachnoid hemorrhage (GASH) is a double-blind, prospective, randomized clinical trial. Recruitment will take place between 2018 and 2019 (Table 1).

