### Safety considerations

An interim analysis will be performed when half of the sample size (40 patients) has completed the follow-up. An independent Data Monitoring Committee (DMC) will decide whether to stop or continue the trial after analyzing the evaluable data.

One of the investigators will have access to patient allocations to monitor possible side effects of glibenclamide, such as hypoglycemia. Capillary glycemia will be checked every 4 h during the 21-day treatment period and all measures to correct hypoglycemia will be taken. During the treatment time, no patients will be discharged.

The DMC will receive all data regarding the use of the drug and the possible side effects, as well the incidence of refractory hypoglycemia (serum glucose levels persistently < 70 mg/dL). If refractory hypoglycemia exceeds a frequency of 40% of treated patients, the trial will be interrupted. The same care will be taken for all other persistent events that are found.

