### Expected outcomes

The primary outcomes will be the distribution of the mRS score assessed after 6 months of the end of the intervention, as favorable (mRS 0–2) and unfavorable (mRS 3–6). Secondary outcomes will be the cognitive assessment and quality of life as measured by the neuropsychological tests, as well as death, delayed ischemic deficits and the occurrence of serious adverse events attributable to medication. These secondary outcomes were preselected to provide supportive evidence related to the primary outcome.

The definition of delayed cerebral ischemia, as elaborated on by Vergouwen et al. [25], is taken as the occurrence of focal neurological impairment (such as hemiparesis, aphasia, apraxia, hemianopia, or neglect), or a decrease of at least 2 points on the Glasgow Coma Scale (either on the total score or on one of its individual components (eye, motor on either side, verbal)). This should last for at least 1 h, is not apparent immediately after aneurysm occlusion, and cannot be attributed to other causes by means of clinical assessment, computed tomography or magnetic resonance imaging of the brain, and appropriate laboratory studies. We will report any serious adverse events and those that were deemed to be related to the trial medication.

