## Project duration and management

Patients will be evaluated by physicians at hospital admission, including intensive care physicians and neurosurgeons, to start complete management for subarachnoid hemorrhage. One of the researchers will apply the inclusion criteria and make the allocation with the randomly selected medication bottle. During the intervention, all adverse effects and neurological status will be recorded by the attending physicians. At the end of the follow-up period, physicians and the neuropsychologist will register the mRS and apply the neuropsychological tests. Once half of the sample is reached, one of the authors, previously selected by the safety committee, will have access to each patient’s allocation to determine the study’s continuity. At the end of the study, all data will be statistically analyzed for group comparisons.

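### Allocation access is described inconsistently: an author with patient-level codes, not only the independent DMC, settles continuation, and unblinded harm monitoring leaves drug-attributed SAEs open to bias

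*Protocol article*

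**What the plan says.** All places are in the Protocol article.

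- **Study design:** the trial "is a double-blind, prospective, randomized clinical trial".
- **Blinding:** patients, investigators, neuropsychologists and clinical staff "are blinded and have no access to the meaning of the coding". The section then says "The only exception to this is one of the investigators", described as "one of the investigators, who had prepared the coded bottles, who will not be blinded and will monitor possible adverse effects".
- **Allocation:** the bottles are made up and coded in the center's pharmacy "by one of the staff members who does not participate in the enrolment process".
- **Safety considerations:** the investigator's access is repeated: "One of the investigators will have access to patient allocations to monitor possible side effects of glibenclamide, such as hypoglycemia". The same section places the decision to stop or continue, after 40 patients have completed follow-up, with an independent DMC, which also receives the drug and side-effect data.
- **Project duration and management:** at the halfway point, "one of the authors, previously selected by the safety committee, will have access to each" patient's allocation, for the purpose of deciding whether the study goes on. The section also has the attending physicians record adverse effects.
- **Expected outcomes:** the secondary outcomes include "the occurrence of serious adverse events attributable to medication". The section adds that any serious adverse event will be reported as well as those judged drug-related. It does not say who makes that judgment.

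**The concern.** Two questions should each have one answer: who can see allocations, and who can stop the trial. The article gives more than one answer to both.

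This affects trial conduct. This is a single-center study, and an author who learns individual allocations midway remains part of the team while enrolment and six-month visits continue. It also affects the harms comparison. Calling an event drug-related is a judgment, and a judge who knows the arm can be influenced by it. The person assigned to look for side effects of glibenclamide is the person who knows who receives it, and nothing in the text keeps that person out of the causality decision.

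**Working it through.** The point depends on no power or event-rate calculation, so the sections are set side by side.

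**1. Who prepared the bottles (Allocation against Blinding).** One section names a staff member at the pharmacy who takes no part in enrolment; the other names an investigator.
- If these are two people, whoever coded the bottles presumably also knows the code, and the declared single exception is incomplete.
- If they are one person, the preparer is an unblinded investigator who also monitors harms.

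Neither section says who holds the code list.

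**2. Who decides on continuation (Safety considerations against Project duration and management).** One names an independent DMC; the other names an author who sees each allocation.
- If the author is the investigator in Blinding, one person prepared the drug, monitors harms knowing the arm, and settles continuation.
- If not, at least two members of the trial team are unblinded, where Blinding allows one.

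On neither reading is the author independent. Selection by the safety committee does not change that.

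**3. When access opens.** Half of 80 is 40. Safety considerations waits for 40 patients with completed follow-up. Project duration and management says only that half the sample has been reached. Trial status (version of 1 May 2019) reports 36 recruited, most still in follow-up. If the second trigger means recruitment, it was 40 − 36 = 4 patients away. Access would then open with 80 − 40 = 40 patients still to enroll and most six-month assessments still to come.

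**4. Whether the harms outcome is exposed.**
- Recording: attending physicians (Project duration and management), who are blinded under Blinding.
- Monitoring: an unblinded investigator (Blinding, Safety considerations).
- Judging causality: nobody named (Expected outcomes).

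The exposure therefore lies in attribution and in any extra scrutiny that the unblinded monitor brings. Routine recording by blinded staff is not itself affected.

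**5. Whether the text requires an unblinded investigator.** Safety considerations describes glucose checks and correction of hypoglycemia without restricting them to one arm. Its interruption rule is counted among treated patients, so someone must know the arms. That section already sends the relevant data to the DMC, which can apply the rule by arm.

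**The case against.** Several counter-arguments have force.

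- **The exception is disclosed.** A reader might infer that an unblinded investigator contradicts the double blind. The documents do not support that: Blinding and Safety considerations both declare the role, so it qualifies the blind. What remains is the author's access, which is undeclared in Blinding unless the two are the same person.
- **The bottle preparer may be one person.** A non-enrolling investigator could be the staff member named in Allocation. That is possible, so this is an inconsistency to clear up, not a proven contradiction. Nor do the documents say that the pharmacy holds the code.
- **The author might only pass data to the DMC.** The wording does not say so; it links the access directly to deciding continuation.
- **Bias in the SAE outcome is not demonstrated.** No section says the unblinded investigator judges causality, blinded physicians record events, and reporting of any SAE is already planned. This stands in full: the outcome is open to bias and no more.
- **Efficacy assessments are protected.** The mRS physician and the psychologists are blinded, and the analysis is said to be blind. This also stands.
- **Someone must know the arms to apply the hypoglycemia rule.** True, but the DMC can do so.

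The point cannot be put down to the brevity of an article. These are positive statements that disagree, and a longer document would have to choose between them.

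**Conclusion.** The concern holds in limited form. The firm part is the conflict between an independent DMC and an author with patient-level allocations over who settles continuation. The account of who prepared the bottles and knows the code is not clearly consistent and needs one statement. The drug-attributed SAE outcome is open to bias because an unblinded investigator monitors harms and no causality judge is named.

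A reader might go further and conclude that the safety comparison is biased, or that the mRS, SF-36 and MoCA results are compromised. The documents do not show either. They give no SAE rate and no attribution rate, so neither the size nor the direction of any bias can be estimated. The conclusion rests on reading the sections as written. If the author and the investigator are one person, the count of exceptions may be right, but the lack of independence remains.

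The correction should come before the interim look, because knowledge of allocation cannot be withdrawn once given.

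**What to change.** 1. **Bottles and code:** amend Allocation and Blinding to name, by role, one person who prepares the bottles and holds the code.
2. **Continuation:** amend Safety considerations and Project duration and management so that the independent DMC alone decides, at one stated trigger. Remove the author's allocation access.
3. **Routine access:** remove the investigator's access from Blinding and Safety considerations. Only the code holder and the DMC then see allocations, and the DMC applies the existing treated-patients rule by arm.
4. **Causality:** state that the blinded attending physicians judge whether an SAE is drug-related.
5. **Safety comparison:** make all SAEs and all hypoglycemia by randomized arm the comparison, with attributed events as supplementary. Expected outcomes already plans to report any SAE, so this mainly changes which measure is named as the outcome.
6. **Disclosure:** report who has already seen allocations and when, since 36 patients were enrolled by version 2.1 and rewording cannot re-blind anyone.

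The cost is an amendment, a short procedure for blinded causality assessment, and a small loss of direct investigator oversight by arm, which passes to the existing DMC. No new staff are needed.

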### Safety considerations

An interim analysis will be performed when half of the sample size (40 patients) has completed the follow-up. An independent Data Monitoring Committee (DMC) will decide whether to stop or continue the trial after analyzing the evaluable data.

One of the investigators will have access to patient allocations to monitor possible side effects of glibenclamide, such as hypoglycemia. Capillary glycemia will be checked every 4 h during the 21-day treatment period and all measures to correct hypoglycemia will be taken. During the treatment time, no patients will be discharged.

The DMC will receive all data regarding the use of the drug and the possible side effects, as well the incidence of refractory hypoglycemia (serum glucose levels persistently < 70 mg/dL). If refractory hypoglycemia exceeds a frequency of 40% of treated patients, the trial will be interrupted. The same care will be taken for all other persistent events that are found.

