### Follow-up

Patients will return after 6 months of follow-up to be evaluated by physicians and psychologists with no knowledge of the treatment allocation. Each patient’s mRS will be assessed by a physician, and psychologists will evaluate quality of life and cognitive performance using the SF-36 questionnaire and the MoCA test.

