### Trial status

This is protocol version 2.1, 1 May 2019. This trial began recruitment on 3 July 2018 and currently has a total of 36 recruited patients. Most of these patients are still in the follow-up period and will soon be interviewed by a psychologist. The recruitment/allocation is anticipated to be complete by 1 August 2019, and the final follow-up should last until 31 December 2019. This submission includes the SPIRIT checklist as Additional file 1.

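### On the article's own dates, the interim stop/continue decision comes too late to limit exposure for most or all of the 80 patients

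*Protocol article*

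**What the plan says.** All references are to the protocol article.

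- **Trigger (Safety considerations):** "An interim analysis will be performed when half of the sample size (40 patients) has completed the follow-up". An independent DMC then decides whether the trial stops or continues.
- **Sample size:** "We estimated a sample size of 80 randomized patients".
- **Follow-up:** "Patients will return after 6 months of follow-up to be evaluated by physicians and psychologists". Expected outcomes counts the period from a later origin: "assessed after 6 months of the end of the intervention".
- **Treatment (Intervention):** one tablet a day until day 21 after the bleed.
- **Trial status (version 2.1, 1 May 2019):** recruitment began on 3 July 2018 and the trial "currently has a total of 36 recruited patients", most of them still in follow-up. "The recruitment/allocation is anticipated to be complete by 1 August 2019".
- **Other safeguards (Safety considerations):** capillary glucose every 4 h throughout treatment, an investigator with access to allocations who watches for side effects, transfer of drug and side-effect data to the DMC, and an interruption rule: "If refractory hypoglycemia exceeds a frequency of 40% of treated patients, the trial will be interrupted".
- **Second account of the halfway look (Project duration and management):** "Once half of the sample is reached", one of the authors, chosen beforehand by the safety committee, sees each patient's allocation to determine whether the study continues.

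**The concern.** The interim sits under the safety heading, and its stated purpose is a decision to stop or continue. Such a decision limits harm only if patients are still being dosed or still to be enrolled. Here treatment lasts about three weeks, the trigger needs six months of follow-up, and recruitment is meant to finish within three months of the version date. The look may therefore arrive when no exposure is left to prevent.

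The section on clinical use in subarachnoid hemorrhage says the drug has not previously been tested clinically in this disease. A between-arm excess of deaths, delayed ischemia or other serious events is what an independent look during dosing would be expected to catch, and this interim is the only DMC decision whose timing the article gives.

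The second account adds uncertainty. It can be read as a recruitment trigger, and it gives access to allocations, for the purpose of deciding continuation, to an author.

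**Working it through.** **Plan's own figure.** 80 / 2 = 40, as stated.

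**Assumptions.** The count of 36 is taken as of 1 May 2019. Accrual is even within each period. The last dose is at most 21 days after enrolment.

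**Accrual rates**
- Observed: 3 July 2018 to 1 May 2019 is 302 days; 36 / (302 / 30.44) = 3.6 per month.
- Needed to close on time: 80 − 36 = 44 patients in 92 days; 44 / (92 / 30.44) = 14.6 per month.

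**Lower bound, if every completion takes 6 months.** The 40th patient is enrolled after 1 May 2019, so 40 completions cannot exist before 1 November 2019, or about 22 November if the 6 months run from the end of treatment. The last patient enrolled on 1 August ends treatment by 22 August. The gap from last dose to interim is at least 71 days.

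**Planned pace.** The 40th is enrolled 4 × 92 / 44 = 8.4 days after 1 May, about 9 May. Adding 6 months gives about 9 November 2019, which is 79 days after 22 August. Randomized and treated by then: 80 of 80.

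**Break-even.** To precede the last dose, the 40th patient had to be enrolled by 22 February 2019, day 234 of recruitment. At the observed rate about 234 × 36 / 302 = 28 patients were enrolled by then.

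**Slower recruitment**

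| Scenario | 40th enrolled | Interim | Randomized at interim | Still to enrol |
|---|---|---|---|---|
| Planned close, 1 August 2019 | 9 May 2019 | 9 Nov 2019 | 80 | 0 |
| Recruitment to 31 Dec 2019 (Table 1 marks recruitment in 2019) | 23 May 2019 | 23 Nov 2019 | about 73 | about 7 |
| Observed pace | about 4 June 2019 | 4 Dec 2019 | about 62 (77%) | about 18 |

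For the last row: 36 + 217 × 36 / 302 = 61.9.

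**Early deaths counted as completed follow-up.** The article does not say whether they are. Assume a share *d* die and count as complete at day 30. The trigger is met when (1 − *d*) × (number enrolled at least 6 months earlier) + *d* × (number enrolled at least 30 days earlier) = 40. On the planned pace:

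| *d* | Interim | Randomized |
|---|---|---|
| 10% | 28 Oct 2019 | 80 |
| 20% | 11 Sept 2019 | 80 |
| 30% | 13 Aug 2019 | 80 |
| 40% (30-day figure in Sample size) | 27 July 2019 | about 78 |

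Check at 20%: 0.8 × 30 + 0.2 × 80 = 40, and the 30th patient was enrolled about 11 March 2019. If deaths count at once instead, the 40% row becomes about 5 July with about 67 randomized.

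The high rows fit poorly with the status report. Under even accrual about 14 of the 36 had passed 6 months by 1 May, leaving 22. For most of the 36 (more than 18) to be still in follow-up, early deaths must be below about 1 − 18/22 = 18%. At 17% the interim falls in late September, with all 80 treated.

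**Look at the end of treatment instead**
- Planned pace: 9 May + 21 days = about 30 May 2019; enrolled 36 + 29 × 44 / 92 = 49.9, so about 30 still to come.
- Observed pace: 33.6 + 21 = 54.6 days after 1 May, about 24 June 2019; enrolled 36 + 54 × 36 / 302 = 42.4, so about 38 still to come.

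**The case against.** **Other safeguards exist during dosing.** This stands. The interruption rule for refractory hypoglycemia carries no date and is not tied to the interim. With glucose checks every 4 h, an unblinded investigator and side-effect data going to the DMC, it can act while patients are being treated. A reader might infer from the calendar that patients have no protection during exposure, or that the interruption rule cannot operate in time. The article does not support that.

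**The DMC may meet at other times.** A charter or full protocol could schedule further reviews, and an article commonly leaves that out. So one can say only that this is the sole DMC decision point whose timing the article states.

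**The claim that nobody could be spared depends on the timetable.** This also stands. Closing on 1 August needs about four times the observed accrual. If recruitment slips, roughly 7 to 18 patients would still be unenrolled at the interim. A reader might infer that the look can protect nobody under any timetable; that holds only if the stated closing date is met.

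**Early deaths may count as completed.** If so, the gap after the last dose shrinks and the two-month figure is not firmly established. At death rates compatible with the status report, the look still falls after all planned treatment.

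**The second account may remove the problem.** If it means half recruited, the look falls about 9 May 2019. If it means half followed up, the triggers agree. The wording allows either, so this is an ambiguity to resolve rather than a proven contradiction or a rescue.

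**Six-month outcomes are harm signals too.** True, which argues for adding an earlier look, and does not require dropping the later one.

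**Conclusion.** The concern holds for the timed interim. On the stated dates the stop/continue decision falls about 9 November 2019, after all 80 patients have finished treatment. At the observed pace it falls about 4 December 2019 with about 77% randomized. It is therefore too late to limit exposure for most or all patients.

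This rests on the count of 36 being current at 1 May 2019, on even accrual, and on follow-up meaning 6 months. Counting from the end of treatment, a later count date or losses to follow-up would delay the look further; counting early deaths as complete would advance it.

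The conclusion does not extend to safety oversight as a whole. Continuous monitoring and the hypoglycemia rule may act earlier, and nothing here judges that rule's threshold. The trigger and decision-maker in Safety considerations and in Project duration and management also need to be reconciled. Priority: should be fixed.

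**What to change.** - In Safety considerations, set the DMC safety look at 40 randomized patients having completed the 21-day treatment period. Supply in-hospital safety data by arm (hypoglycemia, serious adverse events, deaths), with current recruitment status.
- In Project duration and management, state the same trigger and the same decision-maker, and make clear what role, if any, the author with access to allocations has in the decision.
- Check the chosen trigger against the dates in Trial status.

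The cost is amendment wording and an earlier data cut. That look would have no 6-month outcomes; these stay with the final analysis, or with the later look if the sponsor keeps it. The interruption threshold is not addressed.
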